### Ethics and consent form

This study was submitted to and approved by the REC of the institution and will
follow all the norms and precepts of the national and international resolutions,
as described in resolution 466, of December 12, 2012, and complementary
resolutions of the National Council of Health/Ministry of Health. This is a
clinical trial in which interventions to be performed in both arms are
considered physiological by the current literature, respecting the principle of
clinical *equipoise*. All patients must have provided informed
consent before randomization in this study. The informed consent form will be
obtained by the principal researcher, who will be unaware of the allocation
sequence. Such collection may be performed from the patient or legal guardian.
All patients selected for transplantation will be included in the screening of
the study; those eligible according to the inclusion and exclusion criteria will
be informed about the protocol in a standardized way for deciding on
participation, including information about the intervention and possible
laboratory collections. The protocol will be submitted for publication in order
to ensure methods transparency, and the final results will be disclosed to those
involved and sent for publication under peer review, with a description of the
degree of contribution of the authors.

### Study perspectives

According to the updated status on Clinicaltrials.gov, the study is currently in
the randomization phase and has reached 67.8% of the required sample as of
February 28, 2023. Maintaining the current randomization rate, the predicted end
of inclusion will be at the end of the first half of 2023.

## COMMENTS

The present study was designed to evaluate a simple strategy with easy clinical
application for a frequent, morbid and challenging outcome in liver transplantation.
The decision for the primary outcome is based on biological plausibility, avoiding
the previous scientific trend of seeking gross reductions in mortality. We
understand that the single-center design may raise questions regarding the external
validity of the outcomes, although we believe that the construction of
evidence-based medicine occurs by the sum of the different efforts initiated in
physiological and observational studies. The postoperative period following liver
transplantation is an infrequent topic in randomized studies worldwide. We believe
that the study presented here, with its simple and pragmatic description, may help
to promote the current expansion of clinical trials in Brazilian intensive care.

The LIVER-PAM study presented here seeks to understand whether a target of higher (85
- 90mmHg) *versus* lower mean arterial pressure (65 - 70mmHg) for a
period of 24 hours after admission to the intensive care unit for liver
transplantation is sufficient to reduce the incidence of renal dysfunction in this
scenario. Using a single-center, prospective, randomized, controlled and open-label
model, we sought to answer a gap in the management of these patients, who are
infrequently evaluated by randomized clinical trials. If our hypothesis proves to be
true, we will contribute to the description of a potentially safe and inexpensive
tool in the prevention of renal dysfunction following liver transplantation.

## APPENDIX 1 DEFINITIONS OF OUTCOMES

**Protocol:** Comparison between different mean arterial pressure
targets in patients undergoing liver transplantation in an open-label,
controlled, single-center, randomized clinical trial.

□ **Acute renal dysfunction**

Only patients with an increase in serum creatinine by 1.5 times the baseline
value (last value prior to transplantation) will be considered to have renal
dysfunction according to the adaptation of the KDIGO criterion referenced in the
main text. For this, the diuresis criterion was ignored, as it can be difficult
to interpret the real meaning of these data in the postoperative period and in
cirrhotic patients. An increase of 1.5 times was used instead of the criterion
of an increase of 0.3mg/dL because the calculated sample was based on the
criterion of 1.5 times the baseline creatinine.^(1)^

□ **Death within 28 days**

Death within the first 28 days after liver transplantation.

□ **Retransplantation in 28 days**

Conduction of a new liver transplantation within the first 28 days after the
initial transplantation.

□ **Renal replacement therapy in 7 days**

Administration of renal replacement therapy in the first 28 days after liver
transplantation by any modality, prescribed by a specialist team of the
institution itself, based on the classic indications (refractory hyperkalemia,
refractory hypervolemia, refractory acidosis, refractory hypernatremia or
uremia). Patients undergoing renal replacement therapy for ammonia clearance
will not be considered.

□ **Surgical site infection**

Infection at the site of the surgical incision that appears to be related to the
surgical procedure, manifesting as purulent secretion through a drain placed in
the incision of the organ/cavity; organisms isolated from a positive culture of
secretions or tissue of the organ/cavity obtained aseptically; presence of
abscess or other evidence of infection, involving the organ/ cavity, identified
in direct examination, during a new surgery, or through histocytopathological
examination or imaging, which results in surgical approach and/or initiation of
a new regimen of antibiotic therapy, as indicated together by the surgical and
infectious diseases teams.

□ **Days alive and free of renal dysfunction in 7 days**

Number of days during the first 7 postoperative days that the patient was alive
and did not meet the criteria for renal dysfunction consistent with the primary
outcome

□ **Acute renal dysfunction according to urinary NGAL assessment**

Number of days during the first 7 postoperative days that the patient was alive
and did not meet the following criteria for renal dysfunction: urinary NGAL
value > 150ng/mL. This outcome will be assessed at admission and at 48
hours.^(2)^

□ **Primary graft dysfunction - initial poor function subtype at 7
days**

Development of one of the following laboratory criteria within the first 7 days
after liver transplantation: bilirubin > 10mg/dL on the seventh day after
transplantation; international normalized ratio > 1.6 on the seventh day
after transplantation; alanine aminotransferase or aspartate aminotransferase
> 2,000IU/L in any of the first 7 days after transplantation.^(3)^

□ **Primary allograft dysfunction - primarily nonfunctional subtype at 10
days (Broering)**

Need for retransplantation in the first 10 days after transplantation or death
due to a nonfunctioning graft.^(3)^

□ **Major adverse kidney events in 28 days (MAKE28)**

The incidence of death, need for renal replacement therapy or persistent renal
dysfunction at 28 days after liver transplantation.^(4)^

□ **Days alive and hospitalization-free in 28 days**

Number of days among the first 28 postoperative days in which the patient was
alive and hospitalization-free.

□ **Major postoperative bleeding at 7 days**

Dichotomous outcome of bleeding that indicates, on the same day, the transfusion
of more than two units of packed red blood cells or the need for surgical
intervention indicated in the first 24 postoperative hours.

□ **Transfusion of blood components in 7 days**

Number of blood components transfused in 7 days separated into packed red blood
cells (one unit equal to one bag), fresh frozen plasma (one unit equal to one
bag), fibrinogen concentrate (one unit equal to 1g) and tranexamic acid (one
unit equal to 1g).

□ **Arrhythmias requiring chemical or electrical therapy within 7
days**

Description in the prescription or medical records of antiarrhythmic or
electrical cardioversion therapy for the first 7 days for treating abnormal
rhythm. A maximum of one event per patient will be considered dichotomously, as
the same event can be reentrant.

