### Main objective

The primary goal of the study will be to evaluate whether higher (85 - 90mmHg)
*versus* usual MAP levels (65 - 70mmHg) in the first 24 hours
after liver transplantation are associated with a reduced incidence of acute
renal dysfunction at 7 days, according to the adaptation of the KDIGO
criteria,^(15)^ using a
1.5-fold increase in baseline creatinine as a cutoff point (Appendix 1). Patients who die within the first 7 days
will be considered positive for the main outcome measure.

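### The primary renal outcome has no rule for renal replacement therapy, so a 7-day survivor dialysed before creatinine reaches 1.5 times baseline is counted as a non-event

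*Protocol article*

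**What the plan says.** Four places in the protocol article bear on this.

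- **Appendix 1, Acute renal dysfunction.** "Only patients with an increase in serum creatinine by 1.5 times the baseline" value are classed as having renal dysfunction. Two parts of KDIGO are set aside with reasons: "the diuresis criterion was ignored", and "An increase of 1.5 times was used instead of the criterion" of a 0.3 mg/dL rise. RRT is not mentioned.
- **Main objective.** One further route to an event is given: "Patients who die within the first 7 days" "will be considered positive for the main outcome measure".
- **Appendix 1, free-days outcome.** A day counts if the patient was alive "and did not meet the criteria for renal dysfunction consistent with the primary" outcome. There is no RRT rule, and the entry does not say whether the criterion is re-evaluated each day or holds once met.
- **Appendix 1, RRT entry.** RRT is a separate secondary outcome, prescribed by a specialist team "based on the classic indications (refractory hyperkalemia", hypervolemia, acidosis and others). RRT for ammonia clearance is not counted. The heading gives 7 days but the definition gives 28.

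Appendix 1 also makes RRT a component of MAKE28, so elsewhere the plan treats it as a kidney event.

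**The concern.** Dialysis removes creatinine, so values taken after it starts no longer measure kidney function. Several of the listed indications can arise before creatinine has reached 1.5 times baseline. The plan saw that death could hide a renal event and wrote a rule for it, but wrote none for RRT. The same patient can thus be a MAKE28 event and a primary non-event.

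The trial is open-label. The Randomization and blinding section relies on a laboratory-based primary outcome to limit bias. A treatment decision that alters that laboratory value weakens this protection, and the alteration need not be equal in the two arms.

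**Working it through.** **1. Who is misclassified on the primary outcome.** Creatinine is collected daily (Data collection section) and the outcome is incidence over 7 days. Taking the cases in turn:

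- Crosses 1.5 times baseline before RRT: event, whatever dialysis does later.
- Dies by day 7: event.
- Starts RRT below the threshold, never reaches it by day 7, survives: **non-event**.

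Only the third group is affected.

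**2. Size of that group.** The documents give no RRT rate, so both inputs are assumptions: 8-15% start RRT by day 7, and 10-30% of those start below the threshold.

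- Low: 174 × 0.08 × 0.10 = 1.4 patients
- High: 174 × 0.15 × 0.30 = 7.8 patients

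That is about 1-8 of 174, or 0.8-4.5%. Requiring survival to day 7 and no later crossing would make it smaller.

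**3. The plan's own sample size.** Inputs from the Sample size calculation section: 73.7% v 53.7%, alpha 5% (two-sided assumed), power 80%, 1:1. With unpooled variance:

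n = (1.960 + 0.842)² × (0.737 × 0.263 + 0.537 × 0.463) / 0.20² = 86.8, so 87 per arm and **174** in total. The stated figure reproduces. On the pooled two-proportion test, 87 per arm has 78.8% power.

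**4. Effect of misclassification, 87 per arm, pooled test.** Assumed shares missed by the creatinine-only rule:

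*(a) 73.7%/53.7% taken as RRT-inclusive rates; the rule misses some events.*

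| Missed, control / intervention | Observed rates | Difference | Power |
|---|---|---|---|
| 0 / 0 | 73.7 / 53.7 | 20.0 | 78.8% |
| 2 / 2 | 71.7 / 51.7 | 20.0 | 77.9% |
| 5 / 5 | 68.7 / 48.7 | 20.0 | 76.9% |
| 5 / 2 | 68.7 / 51.7 | 17.0 | 63.1% |
| 2 / 5 | 71.7 / 48.7 | 23.0 | 87.9% |

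*(b) 73.7%/53.7% taken as creatinine-only rates; counting RRT adds events.*

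| Added, control / intervention | RRT-inclusive rates | Difference | Power |
|---|---|---|---|
| 2 / 2 | 75.7 / 55.7 | 20.0 | 79.9% |
| 5 / 5 | 78.7 / 58.7 | 20.0 | 81.8% |
| 5 / 2 | 78.7 / 55.7 | 23.0 | 90.5% |
| 2 / 5 | 75.7 / 58.7 | 17.0 | 66.8% |

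With equal shares, the creatinine-only rule costs at most 78.8 − 76.9 = 1.9 points of power under (a) and 81.8 − 78.8 = 3.0 under (b). A 5 v 2 split moves the difference by 3 points, in either direction according to which arm loses more. That split is 87 × 0.05 + 87 × 0.02 = 6.1 patients, within the range in step 2.

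**5. Free days.** If the criterion is applied day by day, a dialysis day with creatinine below the threshold counts as free, even in a patient who crossed it earlier. If the criterion holds once met, only the group in step 1 is affected. The text permits either reading.

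**The case against.** The creatinine-only rule is deliberate and matches the way the 73.7% planning rate was obtained. RRT is not hidden: it is reported as a secondary outcome and within MAKE28. The free-days outcome is secondary and declared exploratory. Putting RRT start into the primary outcome brings a discretionary care decision directly into the endpoint of an unblinded trial. Recruitment had reached 67.8% by 28 February 2023, so the change is more than editorial. All of this stands. It limits the size of the problem and shapes the remedy, but it does not supply the missing rule.

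Three stronger readings are tempting and are not supported.

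- *The most severe renal failure is scored as success.* Patients who cross the threshold before RRT, or die by day 7, remain primary events.
- *The word only contradicts the death rule.* Appendix 1 defines the renal component, and the Main objective adds death to the outcome. The two are compatible.
- *The free-days bias is large against the expected effect.* One might assume 12% on RRT with 3 falsely free days each and obtain 0.12 × 3 = 0.36 day. That is an average over all patients, not a between-arm bias. If equal in both arms, it cancels from the difference. An assumed 15% v 9% would leave 0.06 × 3 = 0.18 day, and the documents support none of these inputs.

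Nor do the documents say that those who decide on RRT know the allocation; the RRT entry names only a specialist team of the institution. The trial is open-label, so differential use cannot be excluded, but it is not shown.

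**Conclusion.** The concern holds in a bounded form. As written, the primary definition gives a wrong classification to 7-day survivors who are dialysed before reaching 1.5 times baseline and do not reach it afterwards. The free-days outcome has the same gap, and a wider one if applied day by day.

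The primary-outcome group is probably small, about 1-8 of 174 under the assumed RRT shares; the documents cannot size it. Equal misclassification has little effect, at most about 3 points of power. Unequal misclassification could move the difference by about 3 points, in a trial with little reserve of power. The sample size of 174 is not in error. The case for acting rests on a clear and correctable gap in a primary definition, not on a demonstrated large bias.

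**What to change.** Make a documented amendment before any outcome comparison. No interim analysis is planned, so this is still credible.

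1. **Primary outcome.** Count as an event, within 7 days, a creatinine rise to the threshold, start of RRT for the indications in Appendix 1, or death. Report the creatinine-plus-death definition, whose creatinine criterion underlies the 73.7%, as a prespecified sensitivity analysis. If the sponsor prefers not to change the primary outcome during recruitment, reverse the two roles.
2. **Free days.** Count every day on RRT as not free, and state whether the creatinine criterion is re-evaluated daily.
3. **Ammonia-clearance RRT.** Do not use creatinine on those days as evidence of no renal dysfunction or of recovery.
4. **RRT entry.** Reconcile the 7-day heading with the 28-day definition before reusing it, and confirm that RRT start and stop dates are captured. The Data collection section lists need for RRT and daily creatinine, but not those dates.

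The cost is an amendment and, if they are missing, retrieval of RRT dates. The downside is that RRT start is a care decision in an unblinded trial and the event becomes slightly wider than the planning definition, so both versions should be shown.

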## INTRODUCTION

Postoperative patient management after liver transplantation is complex and
challenging, as there is an increased risk to the viability of the graft and to the
survival of the patient.^(1)^ In this
scenario, hemodynamic optimization may be a determining factor in the evolution of
the clinical condition.

Renal dysfunction is one of the most frequent postoperative complications after liver
transplantation and is considered the most important predictor of poor long-term
outcome,^(2)^ as it is
associated with higher mortality^(3)^
and impacts the quality of life, as 18.1% of these patients will have a renal
clearance < 30mL/minute/1.73m^2^ within 5 years.^(4)^ This dysfunction is related to a
combination of preoperative (previous renal function, hepatorenal syndrome and
diuretics), intraoperative (ischemia‒reperfusion injury, shock and bleeding) and
postoperative events (nephrotoxic drugs, water balance and hemodynamic
optimization).^(4)^

One of the classical drivers of renal dysfunction is hypoperfusion, which is closely
linked to mean arterial pressure (MAP).^(5)^ The classic target of MAP > 65mmHg is described as the
safety threshold,^(6,7)^ although a trial employing higher MAP levels showed
lower renal dysfunction in certain subgroups of patients with sepsis.^(8)^ In surgical patients, hypotension
is associated with a higher incidence of acute renal dysfunction, and this risk
increases with the length of the insult.^(9,10)^ A reduction in
other postoperative complications has been observed following hemodynamic
optimization for achieving a MAP closer to the patient’s baseline.^(11)^

In the specific scenario of liver transplantation, retrospective data adjusted for
the propensity score inferred the best renal outcome with a MAP >
90mmHg,^(12)^ while a
physiological evaluation indicated that a reduction in renal blood flow occurs below
a MAP threshold of 75mmHg.^(13)^

Preventing renal dysfunction in the postoperative period may represent an important
way to improve short- and long-term patient outcomes, with blood pressure being a
possible therapeutic target. However, there is no definition of the best blood
pressure target and the exact relationship between different blood pressure levels
and renal outcome. In addition, there are currently few randomized clinical trials
in liver transplant intensive care, during which renal dysfunction is more
frequent.^(12)^ Considering

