the current low availability of organs due to the high number of candidate
recipients,^(14)^
understanding tools that may yield better results and reduce complications and
expenses is a priority.

Our hypothesis is that pressure optimization in the first 24 hours after surgery with
higher MAP levels (85 - 90mmHg) is superior to usual care (MAP 65 - 70mmHg) in
preventing acute renal failure in the first 7 days after liver transplantation
surgery.

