### Exclusion criteria

The exclusion criteria were defined with the goals of safety and limiting
confounders, as follows: liver transplantation due to fulminant hepatitis;
liver-kidney transplants; hepatorenal syndrome being treated within 48 hours
pretransplantation; renal replacement therapy in the 15 days prior to
transplantation; persistent refractory shock intraoperatively or on ICU
admission (noradrenaline > 1 mcg/kg/minute associated with a second
vasopressor for more than 2 hours); cardiorespiratory arrest intraoperatively or
on admission; refusal of the physician responsible for the care;
contraindication to the prolonged use of vasopressors; pregnancy; and
retransplantation at an interval of less than 6 months.

Patients or family members will be informed of their right to interrupt the
intervention if they wish to withdraw from participation at any stage of the
study. The team of professionals involved in the care of these patients will be
informed of their rights to interrupt the protocol according to clinical
judgment or in the event of a serious adverse event attributed to the
intervention.

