### Randomization and blinding

Patients will be randomized within 2 hours of ICU admission after liver
transplantation using a simple 1:1 allocation sequence without group
stratification. The randomization will be performed electronically by the
randomization tool of the Redcap® system. The randomization sequence will
be generated *online* and entered into the system by a staff
member who will not participate in the participant tracking process, in
obtaining informed consent from the patient or in the clinical management of the
cases. The researcher will also not participate in the evaluation of the study
outcome data in order to ensure compliance with the allocation concealment
process.

As the interventions in both groups are based on target MAP levels to be followed
by the professionals involved in the care, the authors chose not to blind the
interventions, which, although possible, would be complex to perform in the
center in question. However, the professional responsible for collecting the
outcome data will be an external research nurse, with no affiliation with the
institution where the study is conducted and who is not involved with the care
offered to each patient. The same care will be taken to hire the statistician
who will analyze the results, ensuring that he or she will not be aware of the
allocated groups. To minimize the risk of bias, an objective primary outcome was
chosen based on test results measured by a certified laboratory.

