#### Specific management of the intervention group

The intervention will begin upon admission to the intensive care unit and
will continue for 24 hours after arrival at the ICU. The MAP target of the
intervention group will be 85 - 90mmHg in the first 24 hours after surgery.
The MAP will be measured using an invasive blood pressure catheter, measured
at 1-hour intervals during the first 12 hours and at 2-hour intervals
thereafter until the 24 hours have been completed (according to the protocol
of the ICU). Patients with a MAP lower than the established target may
receive fluids or vasopressors according to the discretion of the attending
physician to achieve the established target MAP.

Noradrenaline will be the initial vasopressor of choice, and the second will
be determined by the attending physician. In hypotensive patients with
reduced cardiac output as monitored by pulmonary artery catheter or
transthoracic echocardiogram, inotropes may be used at the discretion of the
assistant team. Patients who naturally present with a MAP > 90 mmHg even
after complete weaning from vasopressors will not receive additional
vasodilators to reduce the MAP to the study target. The use of vasodilators
in hypertensive patients for the purpose of blood pressure control will be
determined according to the decision of the attending physician.

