### Statistical analysis

The analyses will be performed according to the “intention-to-treat” principle;
all randomized patients will be included in the analysis according to the
treatment group to which they were randomly assigned. Summary statistics per
group, with treatment effects, 95% confidence intervals and p values, will be
presented for the primary and secondary outcomes. Continuous variables will be
tested for normality using the Shapiro‒Wilk test after graphic analysis by
histogram. Parametric continuous variables between two groups will be compared
with the unpaired *t* test and within the same group with the
paired *t* test. If analysis among more than two groups is
required, analysis of variance (ANOVA) will be used. Nonparametric continuous
variables will be evaluated using the Wilcoxon test or the Mann‒Whitney U test
between two groups and the Kruskal‒Wallis test between three or more groups.
Categorical variables will be evaluated using the chi-square test or Fisher’s
exact test, as appropriate. P values < 0.05 will be considered statistically
significant. The outcomes of hospitalization-free days or renal dysfunction over
time will be calculated based on the 7- and 28-day follow-up, respectively,
using Cox regression models. The calculations of survival curves will be
performed with the Kaplan‒Meier method. For the statistical analysis of
outcomes, the results will be adjusted for previous renal function, and logistic
regression will be used to adjust for other confounding factors that generate
inconsistency in the baseline that were not corrected by the randomization of
the study (use of nephrotoxic drugs, maximum tacrolimus level in the first week,
intraoperative fluid balance and intraoperative major bleeding). No statistical
adjustments will be provided for multiple comparisons in the case of secondary
outcomes, and therefore, we suggest that these be interpreted as exploratory
analyses.

The existence of missing data will be described in the publication and managed
with simple exclusion from the analysis. For this study, no interim analyses are
foreseen.

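### AKI already present on ICU arrival counts as a primary event, which dilutes the treatment contrast, and no planned analysis identifies these patients

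*Protocol article*

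**What the plan says.** **Reference and threshold.** Main objective sets a "1.5-fold increase in baseline creatinine as a cutoff point". Appendix 1 (acute renal dysfunction) fixes the baseline: "value (last value prior to transplantation) will be considered to have renal" dysfunction. Neither place sets aside a patient who meets the threshold before the intervention starts.

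**Timing.** Randomization and blinding: "Patients will be randomized within 2 hours of ICU admission after liver" transplantation. Specific management of the intervention group: "The intervention will begin upon admission to the intensive care unit and" it runs for 24 hours.

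**Question.** The hypothesis in the Introduction is about "preventing acute renal failure in the first 7 days after liver transplantation" surgery.

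**What bears on renal state before randomisation.**
- The Introduction attributes this dysfunction to a "combination of preoperative (previous renal function, hepatorenal syndrome and" diuretics), followed by intraoperative causes (ischaemia-reperfusion, shock, bleeding) and postoperative ones.
- The Exclusion criteria remove treated hepatorenal syndrome within 48 hours "pretransplantation; renal replacement therapy in the 15 days prior to" surgery. They also remove combined liver-kidney transplants, refractory shock during surgery or at ICU arrival, and cardiac arrest in the same period.
- Statistical analysis: for the "outcomes, the results will be adjusted for previous renal function, and logistic" regression handles further factors found unbalanced. Those named include nephrotoxic drugs, and fluid balance and major bleeding during surgery.
- Subgroup analysis includes previous renal dysfunction, present or absent.
- Urinary NGAL is measured at admission and at 48 hours.

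**The concern.** The reference creatinine comes before the operation, while randomisation and the MAP target come after it. The protocol itself names intraoperative injury as a cause of the outcome. A patient whose creatinine has already reached 1.5 times baseline on ICU arrival is therefore an event that neither pressure target could have prevented.

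Such patients add the same expected number of events to each arm and pull the two event rates together. At stake is how a null result can be read. Without knowing how many patients were already positive, the trial could not tell apart a MAP target that does not prevent AKI from AKI that largely predated it.

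**Working it through.** **1. The plan's own figure.** Inputs from Sample size calculation: control rate p1 = 0.737, absolute reduction d = 0.20 (so p2 = 0.537), power 80%, alpha 5%. Two-sided testing is assumed, as sidedness is not stated. With unpooled variance:

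n per arm = [p1(1−p1) + p2(1−p2)] × (1.960 + 0.842)² / d² = (0.1938 + 0.2486) × 7.849 / 0.04 = 86.8, so 87 per arm and 174 in total.

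The stated 174 is reproduced. With the pooled-variance test the power at 87 per arm is slightly lower. With mean rate 0.637:

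Φ{[0.20√87 − 1.960√(2 × 0.637 × 0.363)] / √0.4425} = Φ{(1.865 − 1.333) / 0.665} = 78.8%.

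That 79% is the reference for the comparison below.

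**2. Dilution under the current definition.** Let q be the share of all randomised patients already at 1.5 times baseline, equal in both arms. The documents do not give q, so it is assumed. The planned relative effect is r = 0.20/0.737 = 27.1%. A second assumption is that r acts only on events not yet present:

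- intervention rate = q + (0.737 − q)(1 − r)
- visible difference = r(0.737 − q)

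For q = 10%: 0.10 + 0.637 × 0.729 = 0.564, a difference of 17.3 points.

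**3. Holding the 20-point difference instead.** The relative reduction then needed among later events is 0.20/(0.737 − q).

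| q | Visible difference (step 2) | Power, 87 per arm | Total N for 80% (pooled) | Relative reduction needed (step 3) |
|---|---|---|---|---|
| 0 | 20.0 points | 79% | 180 | 27% |
| 5% | 18.6 points | 73% | 206 | 29% |
| 10% | 17.3 points | 67% | 238 | 31% |
| 20% | 14.6 points | 53% | 328 | 37% |

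**4. New AKI in patients below 1.5 times at admission.** Control risk is (0.737 − q)/(1 − q), the intervention risk is that times (1 − r), and the number available is 174(1 − q).

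| q | Patients | Control vs intervention | Power |
|---|---|---|---|
| 5% | 165 | 72.3% vs 52.7% | 74.5% |
| 10% | 157 | 70.8% vs 51.6% | 70% |
| 20% | 139 | 67.1% vs 48.9% | 59% |

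This subset does not restore the planned power. Its value is for interpretation.

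**5. Does any stated element identify these patients?** Previous renal function describes the pre-transplant state. Fluid balance and bleeding during surgery are proxies for injury. The shock and arrest exclusions remove severe insults but not every patient with raised creatinine. NGAL is a different marker with its own cutoff and is planned as an outcome. None classifies a patient by the primary outcome's own criterion at randomisation.

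**The case against.** The strongest reply has four parts.

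- **The design is coherent.** A pre-transplant reference is defensible. The 73.7% comes from the same population and centre under the same 1.5-times rule, so it may already contain such cases. The 20-point target is absolute and chosen for clinical relevance; the protocol claims no relative effect and does not say that every event is preventable. This stands: the 27% model is an assumption, and step 3 of the check is the version that does without it.
- **The share may be small.** Creatinine lags injury, so few patients may cross the threshold by ICU arrival. This stands too. At 5% the loss is 1.4 points of difference and about 6 points of power.
- **Supplementary analyses belong in the analysis plan.** This stands in part. The article does, however, state its exclusions, covariates and subgroups, and that stated set leaves the gap.
- **A pre-intervention creatinine may not exist.** The Data collection section lists daily creatinine and an admission SOFA score, not a named pre-randomisation sample. This limits the fix.

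A reader might infer that the primary comparison is biased. It is not: existing AKI is balanced by randomisation in expectation, and chance imbalance is covered by the test and confidence interval, as for any prognostic factor. A reader might also infer that the protocol ignores injury before the intervention. The exclusions, the intraoperative covariates and admission NGAL show otherwise.

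**Conclusion.** The point holds as one of dilution and interpretability. AKI present on ICU arrival counts as a primary event in either arm, and nothing stated identifies it. The sample size arithmetic is not at fault, and the primary definition need not change.

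The size cannot be fixed from the documents. At assumed shares of 5 to 20%, with a constant 27% relative effect on later events, power falls from 79% to between 73% and 53%; the low end is plausible. It would go too far to say that a conclusion about prevention must rest on the patients free of AKI at admission. The intention-to-treat result remains the primary conclusion, and the subset helps to read it.

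**What to change.** Keep the primary definition, the intention-to-treat set, the sample size and the intention-to-treat result as the primary conclusion. Before unblinding, write into the analysis plan:

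1. The ratio of ICU-admission creatinine (the value used for the admission SOFA) to pre-transplant creatinine, as a covariate in the adjusted model.
2. The number in each arm already at 1.5 times baseline or more at ICU admission.
3. A supplementary analysis of new AKI in patients below 1.5 times at admission.

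Use only a sample drawn at ICU admission. A later first-day value could have been affected by the intervention, and a subset built on it would no longer be protected by randomisation.

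**Cost.** Analysis-plan wording, using a value the trial should already hold. The article reports 67.8% of the sample recruited, no interim analysis and a statistician unaware of allocation, so the additions could be fixed before results are known; after unblinding they would be post hoc. The subset is smaller and less precise (174 × 0.80 = 139 to 174 × 0.95 = 165 patients if 5 to 20% are already positive), and patients without an admission sample cannot be classified; their number should be reported by arm.
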